### Study Integrity

The study design will be guided by the CONSORT statement [52], and randomisation to study condition will occur following the completion of Time 1 assessment. Project staff tracking data collection will be blinded to study condition. Randomisation will occur using block randomisation undertaken by the study manager and concealed from investigators. The intervention protocol will be manualised, and all intervention calls will be audio-taped with a proportion reviewed to ensure adherence to the delivery of the intervention protocol. All analyses will be conducted on the basis of intention to treat.

### Measurement

The majority of study data will be collected at Time 1, Time 2 and Time 3 by computer assisted telephone interview (CATI). Self-reported socio-demographic variables will include gender, age, ethnicity, income, education, employment status, and private health insurance status. Medical information will include co-morbidities and colorectal cancer treatment. Disease variables including cancer grade and stage, as available, will be collected from cancer registry records. To assess the implementation of the intervention, we will measure intervention satisfaction and quality of materials by self-administered questionnaire at Time 2, participant adherence to the intervention and level of contact by data collected from the web-based computer application, and delivery of the intervention components through a health coaching session checklist.

#### Implementation Evaluation

A self-administered satisfaction survey will be used to measure satisfaction with specific aspects of the intervention as well as overall satisfaction with the intervention. Specific questions will address: the content (e.g. relevance and usefulness of topics); the service (e.g. timing and duration of calls, use of the telephone); the relationship with the health coach (e.g. expectations met, feeling comfortable, level of rapport with the health coach); and the intervention materials (e.g. relevance and readability of the handbook and brochures). Participants will also be asked to highlight the strengths and weaknesses of the intervention in two open-ended questions.

The delivery of the intervention will be evaluated by an objective assessor using a criterion based checklist for each health coaching session. The criteria will include assessment of health coaching skills used (e.g rapport building) as well as a checklist against the content objectives for each session (e.g. how well did the coach explain the purpose of the call?). Participant adherence to the intervention and level of contact will be assessed by: the proportion of sessions completed during the intervention period; the topics covered in each session; the total length (minutes) of intervention exposure during the intervention period; and the number of call attempts, missed calls and reasons for missed calls. This data will be recorded by health coaches on a web-based computer application throughout the intervention.

#### Outcome Evaluation

##### Primary outcome variables

###### Physical activity

We will use a modified version of the leisure score index of the Godin Leisure-Time Exercise Questionnaire that has been shown to be a reliable and valid self-report measure of physical activity[45]. The questionnaire contains three questions that assess the average frequency of mild, moderate, and strenuous exercise during free time in a typical week. The modified version of the questionnaire also provides average duration.

###### Cancer-related fatigue

We will use the 13-item Functional Assessment of Chronic Illness Therapy Fatigue Scale (FACT-FS) of the Functional Assessment of Chronic Illness Therapy measurement system which was developed specifically for the cancer population[53,54].

###### Quality of life

We will use the Short Form-36 (SF-36), a widely used measure that has published norms for the Australian general population[55,56]. The SF-36 contains a mental health and physical health summary scale suitable to measure the impact of the intervention on patients' wellbeing, and generates a preference-based utility instrument SF-6D which will be used in the cost-effectiveness analyses.

##### Secondary Outcome Variables

###### Nutrition

We will use the Cancer Council Victoria Food Frequency Questionnaire that shows acceptable levels of reliability and validity when compared with seven-day weighted food records, and has been successfully used over the telephone with cancer survivors[57].

###### Smoking

We will use brief questions about smoking behaviour based on the commonly used Cancer Council New South Wales validated items[46].

###### Weight management

Will be assessed by body mass index (BMI, kg/m^2^) and waist circumference (cm). Participants will be provided with tape measures for measurement of waist circumference.

###### Psychological adjustment

We will use (a) the Brief Symptom Inventory (BSI-18) to assess anxiety, depression and somatisation[58]; (b) the Acceptance and Action Questionnaire (AAQ-II) to assess experiential avoidance and the Mindful Attention Awareness Scale (MAAS)[59] to assess mindfulness; and (c) The post-traumatic growth inventory (PTGI) to assess growth following a cancer diagnosis[60]; and (d) the Functional Assessment of Chronic Illness Therapy Spiritual Well-being module (FACIT-Sp)[61] to measure spirituality.

###### Colorectal cancer specific quality of life and physical symptoms

We will use the Functional Assessment of Chronic Illness Therapy colorectal cancer (FACT-C) to measure quality of life and colorectal cancer-specific symptoms [53,54].

#### Cost Effectiveness

In order to assess the economic value of the intervention, several health outcome variables (detailed above) will be combined with resource data to produce cost-effectiveness ratios at Time 2. Taking a 'health system' perspective, the types of resources in the analyses will include all intervention resources recorded by the study manager (e.g. health coach materials), participant health care utilisation (e.g. hospital admissions), community health resources and medications. Detailed data will be collected by self report and validated with a randomised sub-sample of 20% of patient records and provider surveys. Resources will be valued using nationally applicable sources (e.g. Diagnosis-Related Group codes for hospital admissions and Pharmaceutical Benefits Scheme cost codes for medications). All costs will be aggregated for the control and intervention arms. The primary health benefit for the cost effectiveness analyses will be quality-adjusted life years (QALYs). Quality of life will be measured by the SF-36; the SF6D algorithm will be used to produce QALY-weights on a 0–1 scale. Secondary health benefits will include the mean change in lifestyle factors and health outcomes.

### Data Analyses

Each hypothesis will be tested independently, taking into account hypothesised predictors as well as potential confounding factors (e.g. age, gender). Multiple (linear, multinomial or logistic) regression models will be fitted to consider the relative strength of cross-sectional associations between primary outcome variables (continuous, categorical or dichotomous) and patient characteristics. Repeated-measures regression models will be used to analyse and summarise changes in primary outcome variables over time and to determine the relationships with the various demographic, clinical, lifestyle, and psychosocial characteristics over the three measured time points. The effect of the intervention will be assessed by including a dichotomous variable (control/intervention) in the model, and assessing its interaction with the time-dependent response variable. Repeated-measures regression models will use a generalised estimating equations approach to account for the expected missing data due to attrition over time. Variables measuring health outcomes at Time 1 will be included in subsequent models to control for their effect on health outcomes in later time periods. Exploratory analyses on effect modification and mediation will also be conducted. Effect modification will be assessed through subgroup analyses and the introduction of interaction terms into the models to detect statistical differences between stratum-specific estimates. Standard statistical software including STATA (STATA SE 10.0; StataCorp, College Station, TX), and SPSS (version 14.0 for Windows) will be used for analysis and data management.

For the cost effectiveness analyses, incremental cost-effectiveness rations combining cost and health outcome data will be calculated. The incremental difference in costs between the 2 groups will be divided by the difference in QALY's (and other secondary health benefits) between the groups at Time 2 to generate the incremental cost-effectiveness ratio. This represents the additional cost and health effects of the intervention above the control condition. One-way sensitivity analyses will be undertaken to test the robustness of the ratios to variation in key parameters. Detailed probabilistic (multivariate) sensitivity analysis will be undertaken for all projections and parameters with uncertainty and/or variability using TreeAge Pro 2009 (Healthcare module) software (TreeAge Software Inc, Williamstown, MA, USA).

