## Methods/Design

### Study Design

The study is a two-armed prospective RCT in which approximately 350 colorectal cancer survivors will be randomised in a 1:1 ratio to the intervention or control group using a computer-generated random numbers sequence. Participants in both groups will complete assessments at baseline (Time 1), post-intervention or 6 months follow-up (Time 2), and at 12 months follow-up for longer term effects (Time 3).

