### Study Aims

i. To investigate the effect of a lifestyle intervention on lifestyle factors and health outcomes [primary outcome variables include physical activity, cancer-related fatigue and quality of life] at Time 2 and Time 3.

ii. To assess the cost-effectiveness of study participants receiving the intervention in comparison with participants receiving the control condition.

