Based on our past experience of recruiting colorectal cancer patients with this method, we anticipate approximately 80% of doctors will give permission for patients to be contacted and approximately 60% of patients will consent to participate. We therefore anticipate a final sample size of approximately n = 350 eligible participants (n = 175 in the intervention and control conditions at Time 1). Conservatively allowing for 20% attrition during the intervention, we expect n = 140 subjects per condition at Time 2. Sample size analysis indicated that 130 subjects per condition (intervention and control) or a total of 260 were required to detect, with 80% power and type I error of 5% (two-tailed), a moderate effect size in quality of life of 0.35.

Upon receipt of the completed consent package, all patients will be phoned by the project team to complete a brief screening instrument to assess factors that would exclude participation in the trial (physical activity using the Godin Leisure-Time Exercise Questionnaire [45], fruit and vegetable intake using brief questions developed by the Cancer Council NSW [46], and BMI elicited from self reported weight and height. Telephone interviewers will then complete the Time 1 interview, and computer-generated randomisation to study condition will occur following the completion of the Time 1 interview. Randomisation will be conducted by the project manager and concealed from investigators.

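### Three unranked primary outcomes at two time points, with neither SF-36 summary scale chosen, against a sample size that covers one quality-of-life comparison at 5%

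*Protocol article*

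**What the plan says.** The first aim in Study Aims lists "primary outcome variables include physical activity, cancer-related fatigue and quality of life] at Time 2 and Time 3". The Abstract and the Outcome Evaluation section name the same three outcomes as primary. No section ranks them or says which time point leads.

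Under Quality of life, the instrument is the SF-36: "The SF-36 contains a mental health and physical health summary scale". Neither scale is named as the endpoint.

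Sample Recruitment Procedures sizes the trial on quality of life alone. Its requirement of 130 per arm, 260 in all, rests on "a moderate effect size in quality of life of 0.35", at a two-sided 5% level and 80% power. It expects 175 per arm at Time 1 and, after 20% attrition, 140 per arm at Time 2.

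Data Analyses opens with "Each hypothesis will be tested independently" and goes on to covariates. The treatment effect is assessed through the interaction of group with time in a repeated-measures model fitted by generalised estimating equations. The section gives no ordering of hypotheses and no division of the type I error. It does not say whether the interaction is one joint test per outcome or one contrast per time point.

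**The concern.** Three outcomes at two time points make six comparisons with primary status. Counting both SF-36 summary scales makes eight. The 5% in the sample-size paragraph belongs to one comparison. If separate tests are each made at that level, the chance that at least one primary result is significant when the intervention does nothing exceeds 5%, and the article sets no limit on it. The 80% power likewise describes one quality-of-life score. It says nothing about fatigue or physical activity, and it allows for no correction.

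The Discussion says that a successful intervention could move straight into practice, yet the article does not define success across the primary outcomes. One significant result among several could be read as success, and the error rate of that reading is not the stated 5%.

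**Working it through.** **Inputs from the article.** Two-sided 5%, power 80%, standardised effect 0.35, 1:1 allocation, 130 per arm required, 140 per arm expected at Time 2; three primary outcomes, two follow-up times, two SF-36 summary scales.

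**Assumptions, not in the article.** Each test is made at 5%. Test statistics correlate 0.2-0.7 between outcomes and 0.5-0.7 between time points. The correlation between the Time 1 and Time 2 scores is 0.4-0.6.

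**Step 1: the plan's own figure.** n per arm = 2(1.960 + 0.842)² / 0.35² = 2 × 7.85 / 0.1225 ≈ 128.2, so 129. The t-test version gives 129.1, so 130. Power at 130 per arm is 80.6% (normal) or 80.3% (t). The stated 130 reproduces for one test, with no allowance for others.

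**Step 2: independent tests.** The chance of at least one false positive among k tests is 1 − 0.95^k:

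| k | Reading | Chance |
|---|---|---|
| 3 | one joint test per outcome | 14.3% |
| 4 | the same, both SF-36 scales | 18.5% |
| 6 | three outcomes, each time point tested | 26.5% |
| 8 | four scores, each time point tested | 33.7% |

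**Step 3: correlated tests.** The same patients supply every outcome at every time, so independence gives upper values. Multivariate-normal simulation (400,000 draws, two-sided 5% per test, outcome-by-time product correlation) gives:

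- One test per outcome: 10.9-13.6% for three outcomes and 13.0-17.4% for four, at outcome correlations of 0.7 down to 0.3. At 0.2 the values are 14.0% and 18.0%. Simulating the joint two-degree-of-freedom test directly gives the same range, about 11-18%.
- Each time point tested: 17.7% (outcomes 0.7, times 0.7) to about 24% (outcomes 0.2, times 0.5) for six tests; 20.9% to about 31% at the same two corners for eight.

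**Step 4: power under a correction.** At 140 per arm and effect 0.35, the expected test statistic is 0.35 × √70 = 2.928.

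- One test at 5%: Φ(2.928 − 1.960) = 83% (t-test 83.1%).
- First Holm step over three outcomes, alpha 0.05/3 = 0.0167: Φ(2.928 − 2.394) = 70% (t-test 69.8%).
- The same step with Time 1 adjustment, Φ(0.35 × √(70/(1 − ρ²)) − 2.394): 79% at ρ = 0.4, 84% at 0.5, 90% at 0.6.
- Evaluable patients per arm for 80% power at alpha 0.0167 without adjustment: 2(2.394 + 0.842)² / 0.1225 ≈ 171, against 140 expected.

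**The case against.** Several points on the other side are sound.

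- **The level per test is not stated.** The 5% appears only in the sample-size sentence. Every error rate above is conditional on its use for each test.
- **The independence sentence is about modelling too.** It continues into predictors and confounders, and the Background states only two broad hypotheses. It may mean no more than separate models. That weakens it as proof of six or eight full-level tests, but it supplies no ranking either.
- **The interaction may be one joint test per outcome.** That reading brings the figure down to about 11-18%, still at least twice 5%.
- **The time point for power is fairly clear.** The 130 required is set beside the 140 expected at Time 2, so only the SF-36 scale is truly unnamed.
- **An analysis plan, not shown, could add a multiplicity rule.** The absence of such a rule from an article is not the point here. What the article does fix is three co-equal primary outcomes, two time points, separate testing and sizing on one outcome. A later correction would use power that the sample-size paragraph has not budgeted.

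A reader might infer that the trial will declare success on whichever comparison is significant, with a false positive chance of up to about a third. The documents do not support that. No rule that any one result suffices is stated, the outcomes are distinct and could each carry a separate claim, and 33.7% needs eight mutually independent tests, which measurements on the same patients will not be.

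**Conclusion.** The point stands in conditional form. The article gives equal primary status to more comparisons than its 5% error and 80% power describe, and it does not identify the SF-36 score that was powered. If each test is made at 5%, the chance of at least one false positive primary result is about 11-18% with one joint test per outcome (three or four tests). With each time point tested separately it is about 18-31% under the assumed correlations, and at most 26.5% (six tests) or 33.7% (eight) under independence. The conclusion that it exceeds 5% holds in every case examined; the exact size depends on correlations and a test form that the article does not give. This is worth correcting before outcome data are seen, but it is not a defect that must be resolved for the trial to be sound: the sample-size calculation is right for the comparison it addresses.

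**What to change.** **Preferred.** Name one SF-36 summary score at Time 2, the comparison the trial is sized for, as the single primary outcome. Make the other summary score, fatigue, physical activity and all Time 3 comparisons secondary. The sample size then stands as written, with about 83% power at 140 per arm. The cost is that two outcomes and Time 3 lose primary status, which changes the first study aim and not only its wording.

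**Alternative.** Keep the three outcomes at Time 2, with one SF-36 summary score named, and test them by Holm at an overall two-sided 5%, with Time 3 secondary. Restate the power: about 70% unadjusted at 140 per arm for the first Holm step, or about 79-90% with Time 1 adjustment if the baseline correlation is 0.4-0.6. Data Analyses already includes Time 1 values in the later models, but the correlation is an assumption to be justified from earlier data. The cost is a stricter first threshold for each outcome, and a real loss of power if the baseline correlation is low.

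Under either option, say which score and time point the 80% power refers to, and whether the treatment effect is judged by a contrast at Time 2 or by a joint group-by-time test.

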The intervention includes an evidenced-based approach with strategies drawn from the core components of Acceptance and Commitment Therapy (ACT) [24-27]. ACT is an empirically based third generation cognitive behavioural approach that uses acceptance and mindfulness strategies, and commitment and behaviour change strategies to produce psychological flexibility: the ability to defuse from difficult thoughts and accept difficult feelings while persisting in values-based action [24-28] Psychological flexibility is established through six core ACT processes: acceptance, cognitive defusion (changing our relationship with thoughts), being present, self-as-context, values and committed action [26]. The approach explicitly teaches strategies designed to increase tolerance in the service of goal-directed behaviour, such as healthy eating and physical activity.

Importantly, we are not trialling a psychotherapeutic intervention; rather ACT strategies are used to enhance positive lifestyle behaviours. We propose that ACT provides an alternative to existing intervention approaches for cancer survivors, using specific strategies to overcome internal barriers to making lifestyle improvements by emphasizing the role of emotions and thoughts in the maintenance of good self-management of lifestyle factors. To date, ACT interventions have been successfully used to enhance quality of life and promote positive lifestyle behaviours for a range of health conditions including diabetes [29,30], chronic pain [31], smoking [32], epilepsy [33], and obesity or weight management [34-38].

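### The model that carries the intervention term is not limited to Time 1 lifestyle and psychosocial covariates; if Time 2 or Time 3 values enter, it no longer estimates the intention-to-treat effect

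*Protocol article*

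**What the plan says.** All of the relevant modelling text is in Data Analyses in the protocol article.

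- Repeated-measures regression, fitted by generalised estimating equations, is to describe change in the primary outcomes and to determine their "relationships with the various demographic, clinical, lifestyle, and psychosocial characteristics over the three measured time points".
- The next sentence reads: "The effect of the intervention will be assessed by including a dichotomous variable (control/intervention) in the model". It goes on to an interaction with the time-dependent response, which I read as group by time.
- The only adjustment given a date is for Time 1 values of health outcome variables. The confounders named as examples are age and gender.
- Mediation is listed separately, as exploratory.

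Other sections bear on what the covariates are. Background says that "ACT strategies are used to enhance positive lifestyle behaviours". The Intervention section names symptom management, psychosocial support and lifestyle support as the content of the programme. Physical activity is a primary outcome. The secondary outcomes include BMI, distress (BSI-18), mindfulness and "the Acceptance and Action Questionnaire (AAQ-II) to assess experiential avoidance". Measurement says that most data are collected at all three times. Study Integrity commits every analysis to intention to treat.

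**The concern.** Activity, diet, weight, distress, experiential avoidance and mindfulness at Times 2 and 3 are measured after randomisation, and the programme sets out to move them. In a randomised comparison they are not confounders. They are possible mediators, and several are outcomes.

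A model for fatigue or quality of life that conditions on them estimates whatever part of the effect does not pass through them. Even that holds only if nothing unmeasured drives both the covariate and the outcome. The total effect of assignment is what intention to treat calls for, and this model would not give it. An intervention that works by its intended route could look weak or null. Two analysts following the same text could also fit different models and report different primary results.

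**Working it through.** **1. What the text fixes.** The sentence on the intervention indicator refers to the model. The nearest model before it is the repeated-measures one that carries the lifestyle and psychosocial characteristics, and no other effect model is described. The sentence about Time 1 adjustment covers health outcomes. Study Aims and Cost Effectiveness treat lifestyle factors and health outcomes as two separate classes, so that sentence does not limit lifestyle covariates to Time 1. Post-randomisation adjustment is therefore allowed by the text, although it is not spelled out.

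**2. Reproducing the plan's own figure.** Inputs from Sample Recruitment Procedures: two-sided 5%, 80% power, "a moderate effect size in quality of life of 0.35", and "130 subjects per condition (intervention and control) or a total of 260 were required".

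- n per arm = 2(1.960 + 0.842)² / 0.35² = 128.1, rounded up to 129. The t-test version gives 129.1, rounded up to 130. The stated figure is reproduced.
- "Conservatively allowing for 20% attrition during the intervention, we expect n = 140 subjects per condition at Time 2": 175 × 0.8 = 140.
- Power = Φ(d√(n/2) − 1.96). At n = 130: Φ(0.35 × 8.062 − 1.96) = Φ(0.862) = 80.6%. At n = 140: Φ(0.35 × 8.367 − 1.96) = Φ(0.968) = 83.4%.

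**3. Illustration if mediators are adjusted for.** The mediated share f is an assumption; the documents give none. With no mediator-outcome confounding, and ignoring any change in residual variance or precision, the coefficient becomes 0.35(1 − f).

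| f | coefficient (SD) | power at 140 per arm |
|---|---|---|
| 0 | 0.350 | 83% |
| 10% | 0.315 | Φ(0.676) = 75% |
| 25% | 0.2625 | Φ(0.236) = 59% |
| 50% | 0.175 | Φ(−0.496) = 31% |
| 75% | 0.0875 | Φ(−1.228) = 11% |

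**4. Is the direction certain?** I used a least-squares simulation with 400,000 participants and a true total effect of 0.35. In the main scenarios the intervention shifts the mediator by 0.5, the mediator acts on the outcome with slope 0.35, and the direct effect is 0.175 (0.5 × 0.35 + 0.175 = 0.35). An unmeasured common cause U acts on the mediator with slope m and on the outcome with slope y. The mediator's variance given group and its Time 1 value is 0.75, so the adjusted coefficient should be 0.175 − 0.5 × m × y / 0.75.

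| Scenario | Time 1 covariate only | later mediator added |
|---|---|---|
| Half mediated, no U | 0.347 | 0.173 |
| Half mediated, U same direction (m = 0.5, y = 0.5) | 0.352 | 0.008 |
| Half mediated, U opposite (m = 0.5, y = −0.5) | 0.351 | 0.343 |
| Half mediated, U strongly opposite (m = 0.6, y = −0.7) | 0.349 | 0.453 |
| Intervention does not move the mediator | 0.351 | 0.348 |
| Intervention moves the mediator the wrong way (−0.2; direct effect 0.42) | 0.348 | 0.418 |

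For the four half-mediated rows the formula gives 0.175, 0.008, 0.342 and 0.455, which agrees with the simulation. Adjustment for Time 1 values keeps the total effect in every scenario. Adding the later value can shrink it, leave it nearly unchanged or inflate it.

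**The case against.** The strongest reply is that the article never says Time 2 or Time 3 covariate values enter the effect model. The phrase about three time points can describe the repeated outcome. The models are in the plural and serve two purposes. Demographic and clinical characteristics are mostly fixed at Time 1. The dated adjustment is to Time 1, the example confounders cannot be affected by treatment, and mediation is kept apart as exploratory. All of this makes a Time 1 reading possible, and that part of the reply stands. A reader might infer that the model definitely holds post-randomisation covariates; the document does not support saying so.

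A second reply is that a condensed article may leave its covariate list to an analysis plan that is not shown. That is right for a list. Here, however, the article itself describes the model's content and then puts the group term into it, so the point concerns what is stated.

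A third reply is about direction and size. A reader might infer that the estimate must be biased toward zero, or that the article's theory implies a large mediated share. Neither follows. The simulated coefficients run from 0.01 to 0.45 around a true 0.35, and Background describes a mechanism without quantifying it. The power figures also apply only to the quality-of-life effect used for the sample size. Physical activity is itself a primary outcome, so the same chain does not carry over to it unchanged.

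**Conclusion.** The point holds as a defect in how the effect model is described. The text puts the intervention term into a model with lifestyle and psychosocial characteristics, and does not confine those covariates to Time 1. If later values are used, the group-by-time coefficient is not the intention-to-treat effect.

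Attenuation is the likely consequence if the intervention works through these variables, but it is not guaranteed. The fall in power from 83% to about 75%, 59% or 31% rests on assumed mediated shares of 10%, 25% or 50%, on no mediator-outcome confounding and on unchanged residual variance. It is an illustration and not an estimate for this trial. The wording should be settled before the outcome data are analysed.

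**What to change.** State in Data Analyses that the model estimating the intervention effect contains only:

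- group, time and group by time;
- the Time 1 value of the outcome;
- a short prespecified set of Time 1 covariates, for example age and gender.

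Add that no variable measured after randomisation enters this model as a covariate. Time 2 and Time 3 lifestyle and psychosocial values stay in the exploratory mediation analysis and the descriptive association models, both of which are already planned.

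The cost is one or two sentences. No data collection, sample size or software changes.

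### The stated test of the intervention is not a definable model term; one natural repair is valid but gains nothing from the Time 1 covariate, the other tests only whether the effect changes between 6 and 12 months

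*Protocol article*

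**What the plan says.** Study Aims, aim i, asks how the intervention affects behaviour and health, and lists the main measures and visits: "primary outcome variables include physical activity, cancer-related fatigue and quality of life] at Time 2 and Time 3". The quantities wanted are therefore between-group effects at 6 and at 12 months.

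Data Analyses plans repeated-measures regression by generalised estimating equations (GEE). These models are to describe change in the primary outcomes across all three assessments. A control/intervention indicator is added, and the effect is to be judged by "assessing its interaction with the time-dependent response variable". The same paragraph adds: "Variables measuring health outcomes at Time 1 will be included in subsequent models to control for their effect on health outcomes". The outcomes meant there are those of the later assessments.

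Sample Recruitment Procedures gives a requirement of 130 per arm, 260 in all, calculated "with 80% power and type I error of 5% (two-tailed), a moderate effect size in quality of life of 0.35". On dropout it states: "Conservatively allowing for 20% attrition during the intervention, we expect n = 140 subjects per condition at Time 2".

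**The concern.** The sentence that fixes the test of aim i does not describe a model term. A regressor can interact with another regressor, such as time, but not with the response being modelled. Group by time is presumably meant.

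That repair leaves open whether Time 1 is a response, a covariate or both, and the answer changes what the interaction measures:

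- **All three assessments are responses, and Time 1 is also a covariate.** With time as categories, the interaction is the between-arm difference in change from Time 1. A covariate that is constant within a person cancels from a within-person contrast, so the promised control for Time 1 does not sharpen this test.
- **Only Time 2 and Time 3 are responses, and Time 1 is a covariate.** The interaction is the Time 3 effect minus the Time 2 effect. It is zero when a benefit is fully sustained.

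Two analysts following the paragraph could therefore report intervention effects that answer different questions. The first choice also gives up precision available from a baseline that the trial already collects.

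**Working it through.** **Inputs from the protocol article.** Standardised effect 0.35, two-sided 5%, 80% power, 130 required per arm, 1:1 allocation, and 175 × 0.8 = 140 per arm expected at Time 2.

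**Assumptions.** SD 1 at each visit; a common correlation rho between visits, which the document does not give, so 0.3 to 0.7 is shown; and 140 per arm at Time 3 too, because no Time 3 attrition is stated.

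**1. The plan's own figure.** n per arm = 2 × (1.96 + 0.8416)² / 0.35² = 128.1, so 129. The t-based solution is 129.1, so 130. Power at 130 per arm is 80.6%. The stated figure reproduces. It is the calculation for comparing two means at one time point, with variance 1.

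**2. Three assessments as responses.** Per-person variance is 2(1 − rho) for the change contrast and 1 − rho² for the baseline-adjusted difference. The ratio is 2(1 − rho)/(1 − rho²) = 2/(1 + rho). Power = Φ(0.35 × √(140/(2v)) − 1.96), where v is the relevant variance.

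| rho | v, change | v, adjusted | variance ratio | power, change | power, adjusted |
|---|---|---|---|---|---|
| 0.3 | 1.40 | 0.91 | 1.54 | 70% | 87% |
| 0.5 | 1.00 | 0.75 | 1.33 | 83% | 92% |
| 0.7 | 0.60 | 0.51 | 1.18 | 97% | 98% |

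For example, at rho 0.3 the change contrast gives 0.35 × √(140/2.8) − 1.96 = 0.515, and Φ(0.515) = 0.697.

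The change contrast has 80% power at 140 per arm when v = 70 × (0.35/2.8016)² = 1.09, which is rho of about 0.45. Below that it misses the planned power. For 80% power it needs 128.1 × 1.4 = 180 per arm at rho 0.3 and 128.1 × 1.2 = 154 at rho 0.4. The first exceeds even the 175 to be randomised per arm. The adjusted difference needs 117, 97 and 66 at rho 0.3, 0.5 and 0.7, always below 130.

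**3. Time 2 and Time 3 only as responses.** The interaction estimates d3 − d2 (the Time 3 and Time 2 effects), with variance 2(1 − rho) per person.

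- Sustained effect (0.35 and 0.35): d3 − d2 = 0, so the rejection rate is 5%.
- Effect halved by Time 3 (0.35, then 0.175): at rho 0.5, 0.175/√(2/140) − 1.96 = −0.50, so power is 31%; at rho 0.7 it is 47%.

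**4. Check by simulation.** 400 trials, GEE with exchangeable working correlation, complete data, rho 0.5, 140 per arm, effect 0.35 at both follow-ups.

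- Three-assessment model, group by Time 2: mean 0.357, SE 0.119, the same with and without the Time 1 covariate (largest coefficient difference below 1e-15).
- Time 2/Time 3 model, interaction: mean 0.000, rejecting in 5.0% of trials.
- Same model, group term with Time 2 as the reference visit: mean 0.351, SE 0.103, rejecting in 91.5%.

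**The case against.** The strongest reply is that the wording is a slip and the analysis behind it is sound. The section speaks of change over all three assessments, which favours Time 1 as a response. On that reading, randomisation makes the group-by-time contrast an unbiased estimate of exactly what aim i asks for. Loss of precision is not failure to estimate, and from rho 0.5 upwards the contrast still exceeds 80% power at 140 per arm. This stands. A reader might infer that the planned test cannot estimate the aim i effect; the document does not support that.

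A reader might also infer that a lasting benefit would be declared ineffective about 95% of the time. That needs the less well supported reading plus a rule that only the interaction counts. The plan enters the group variable as well, and in the Time 2/Time 3 model that term gives the Time 2 effect. This stands too, with a limit: the sentence points the assessment at the interaction, and in a three-assessment model with Time 1 as reference the group term describes Time 1, not an intervention effect.

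Three smaller points:

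- The baseline sentence may describe separate models of later outcomes adjusted for Time 1. That is close to the fix below, but the text does not say so.
- The exact cancellation needs complete data. In a simulation with 175 per arm, 20% random dropout and rho 0.5, the coefficients with and without the covariate differed by up to 0.03, with no gain in precision. The practical point is unchanged.
- A journal article may leave the coding of time to an analysis plan. The point here is not a missing detail: the article states a test, and the test as stated is undefined.

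**Conclusion.** The point holds as one of definition and efficiency. The stated test is not a model term, and the role of Time 1 is unresolved. On the better-supported reading the repaired test is valid but has 1.18 to 1.54 times the variance of the baseline-adjusted difference for rho 0.7 down to 0.3, and falls below the planned 80% power when rho is under about 0.45. On the other reading the interaction addresses persistence of the effect, and would miss a sustained benefit only if it were the sole test.

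The sizes rest on an assumed common correlation, SD 1, and 140 per arm with complete data at both follow-ups. The calculation of 130 per arm is correct and is not called into question.

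**What to change.** Replace the interaction sentence and the baseline sentence with one specification, for example:

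> For each primary outcome, the Time 2 and Time 3 values are the responses in a GEE model containing group, time (as categories), group by time, and the Time 1 value of the same outcome. The intervention effect is the adjusted between-group difference at Time 2 and at Time 3, each with its confidence interval. The group-by-time interaction describes whether the effect changes between visits and is not used alone as the test of effectiveness.

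A model of all three assessments with the two arms' Time 1 means constrained to be equal would serve the same purpose. Ranking Time 2 above Time 3 is optional, since aim i names both without ordering them.

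The cost is wording only: the same data, participants and software, and no change to the sample size.
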